### **3.1.6 Post-dosing Follow-up Period**

Subjects who discontinue the study early, or those who reach Week 96 and choose not to continue to receive BMS supplied study drug via the methods described in [Section 3.2](#), are required to enter a post-dosing follow-up period to be seen for a safety visit 12 weeks after discontinuation.

### **3.1.7      *End of the study***

The end of the study will occur when the last study visit has been completed, defined as the final subject completing their final study visit (expected to be 12 weeks after a Week 96 or Early Termination visit for subjects required to complete the post-dosing follow-up period).

The study design schematic is presented in [Figure 3.1.7-1](#).

**Figure 3.1.7-1: Study Design Schematic**

[figure not shown]

-  Subjects with Hemoglobin < 11.0 g/dL should be excluded from participation in the optional Week 2 Intensive PK visit.
-  Virologic Futility will be evaluated (see [Section 8.4.7](#))
-  The selection of the Continuation Dose will be made using the Week 24 data. If selection of the Continuation Dose cannot be made using the Week 24 data, the assessment will be made using Week 48 data.
-  Subjects who discontinue the study early, or who reach Week 96 but choose not continue with BMS supplied study drugs via the methods described in [Section 3.2](#), are required to be seen for one visit 12 weeks after end of study treatments.

### **3.2 Post Study Access to Therapy**

At the conclusion of the study, subjects who continue to demonstrate clinical benefit will be eligible to receive BMS supplied study drug. Study drug will be provided via an extension of the study, a rollover study requiring approval by responsible health authority and ethics committee or through another mechanism at the discretion of BMS. BMS reserves the right to terminate access to BMS supplied study drug if any of the following occur: a) the marketing application is rejected by responsible health authority; b) the study is terminated due to safety concerns; c) the subject can obtain medication from a government sponsored or private health program; or d) therapeutic alternatives become available in the local market.

### **3.3 Study Population**

For entry into the study, the following criteria **MUST** be met.

#### **3.3.1 Inclusion Criteria**

##### **1. Signed Written Informed Consent**

- a) Ability to understand and sign a written informed consent form

##### **2. Target Population**

- a) Antiretroviral treatment-naïve; defined as no current or previous exposure to > 1 week of an antiretroviral drug
- b) Plasma HIV-1 RNA  $\geq$  1000 copies/mL
- c) CD4 T-cell count > 200 cells/mm^3
- d) Fully susceptible to study drugs EFV, TDF, FTC as seen on Screening genotype/phenotype report(s)
- e) Estimated Life expectancy  $\geq$  1 year
- f) Subject Re-enrollment: This study permits the re-enrollment of a subject that has discontinued the study as a pre-treatment failure (ie, subject has not been randomized / has not been treated). If re-enrolled, the subject must be re-consented and assigned a new PID. Re-enrollment is limited to one occurrence.

##### **3. Age and Reproductive Status**

- a) Males and non-pregnant females
- b) At least 18 years of age, (or minimum age as determined by local regulatory or as legal requirements dictate)
- c) Willingness to use approved highly effective methods of contraception (see below) to avoid pregnancy (female subjects who are WOCBP and male subjects who are sexually active with WOCBP)
- d) Women of childbearing potential (WOCBP) must have a negative serum or urine pregnancy test (minimum sensitivity 25 IU/L or equivalent units of HCG) within 24 hours prior to the start of study drug

- e) Women must not be breastfeeding
- f) WOCBP must agree to follow instructions for method(s) of contraception for the duration of treatment with study drug BMS-955176 plus 12 weeks post-treatment completion
- g) Males who are sexually active with WOCBP must agree to follow instructions for method(s) of contraception for the duration of treatment with study drug BMS-955176 plus 5 half-lives of the study drug BMS-955176 (8 days) plus 90 days (duration of sperm turnover) for a total of 98 days post-treatment completion
- h) Azoospermic males and WOCBP who are continuously not heterosexually active are exempt from contraceptive requirements. However WOCBP must still undergo pregnancy testing as described in this section

Investigators shall counsel WOCBP and male subjects who are sexually active with WOCBP on the importance of pregnancy prevention and the implications of an unexpected pregnancy. Investigators shall advise WOCBP and male subjects who are sexually active with WOCBP on the use of highly effective methods of contraception.

All subjects must agree to the use of a highly effective method of contraception as listed below. In addition male subjects should use condoms during treatment and for 98 days following the last treatment when relevant systemic exposure is no longer present.

#### **HIGHLY EFFECTIVE METHODS OF CONTRACEPTION**

Highly effective methods of contraception have a failure rate of  $< 1\%$  when used consistently and correctly. WOCBP and female partners of male subjects, who are WOCBP, are expected to use one of the highly effective methods of contraception listed below.

Study subjects who are WOCBP cannot use hormonal methods of contraception as one of the highly effective methods of contraception because there are data to show a lack of effectiveness of systemic hormonal contraceptives in women taking BMS-955176. However, WOCBP can continue to use hormonal contraceptives, if necessary, in addition to one other non-hormonal highly effective methods of contraception.

Male subjects must inform their female partners who are WOCBP of the contraceptive requirements of the protocol and are expected to adhere to using contraception with their partner. Relevant exposure of BMS-955176 in female partners of male participants in the study is expected to be negligible. Female partners of male subjects participating in the study may use hormone based contraceptives as one of the acceptable methods of contraception because exposure to the investigational product would be too small to alter exposure of hormonal contraceptives.

1. Nonhormonal IUDs, such as ParaGard®
2. Bilateral tubal occlusion
3. Vasectomised partner with documented azoospermia 90 days after procedure

- Vasectomised partner is a highly effective birth control method provided that partner is the sole sexual partner of the WOCBP trial participant and that the vasectomised partner has received medical assessment of the surgical success.
- 4. Complete abstinence
  - Complete abstinence is defined as the complete avoidance of heterosexual intercourse when this is the preferred lifestyle of the patient.
  - Complete abstinence is an acceptable form of contraception for all study drugs and must be used throughout the duration of study and for the duration of time as specified above.
  - It is not necessary to use any other method of contraception when complete abstinence is elected.
  - Subjects who choose complete abstinence must continue to have pregnancy tests.
  - Acceptable alternate methods of highly effective contraception must be discussed in the event that the subject chooses to forego complete abstinence.

The reliability of sexual abstinence needs to be evaluated in relation to the duration of the clinical trial and the preferred and usual lifestyle of the subject.

At a minimum, subjects must agree to the use of two methods of contraception, with one method being highly effective and the other method being either highly effective or less effective as listed below:

#### **LESS EFFECTIVE METHODS OF CONTRACEPTION**

- Diaphragm with spermicide
- Cervical cap with spermicide
- Vaginal sponge with spermicide
- Male or female condom with or without spermicide\*
- By male subject's WOCBP partner only: Progestogen-only oral hormonal contraception, where inhibition of ovulation is not the primary mode of action.

\* A male and female condom must not be used together

### **3.3.2 Exclusion Criteria**

#### **1. Target Disease Exceptions**

- a) Resistance or partial resistance to any study drug determined by tests at Screening
- b) Current or historical genotypic and/or phenotypic drug resistance testing showing resistance to EFV: K103N, L100I, K101E/P, V106A/M, Y181C/I/V, Y188L/C/H, G190A/S/E, or M230L
- c) Current or historical genotypic and/or phenotypic drug resistance testing showing resistance to TDF: K65R or T69ins
- d) Current or historical genotypic and/or phenotypic drug resistance testing showing resistance to FTC: M184I/V or Q151M

- e) Current or historical genotypic drug resistance testing showing any of the following non-accessory thymidine analogue mutations (TAMs): M41L, D67N, K70R, L210W, T215Y/F, K219Q/E
- f) Current or historical genotypic drug resistance testing showing primary protease inhibitor resistance mutations: I50L, I84V/A, N88D/S, I47A/V, V82A/F/T/S. These exclusionary mutations are listed only in order to allow subjects who develop on-treatment emergent virologic resistance a subsequent PI-based regimen (after study discontinuation)

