**Figure 1.1.2-1: Simulated Maximum Viral Load Decline from Baseline Under Fed Conditions**

[figure not shown]

 Solid lines are 10th and 90th percentiles and the median of simulated data, shaded area is the 90% confidence interval of simulated data, vertical solid lines are the 25th to 75th percentile of the simulated steady state BMS-955176 Cmin for the 60 mg MC tablet dose, vertical dotted lines are the 25th to 75th percentile of the simulated steady state BMS-955176 Cmin for the 120 mg MC tablet dose, and vertical dashed and dotted lines are the 25th to 75th percentile of the simulated steady state BMS-955176 Cmin for the 180 mg MC tablet dose.

While baseline EC90 was not a covariate included in the model due to the lack of significance; this covariate, among others, was considered marginally significant and it is possible this covariate will become important with additional data. This Phase 2b clinical trial will enroll subjects regardless of their viral susceptibility to BMS-955176; a range of baseline EC90s are anticipated, and therefore the three doses above will give a wide range of exposures and coverage to assess against a range of baseline susceptibilities. Thus, the three doses of BMS-955176 may demonstrate varying rates of antiviral efficacy in Arms 1-3. Additionally, these three doses of BMS-955176 will allow for an assessment of safety and tolerability over a wide range of exposures by providing observed longer term clinical data. The combined efficacy and safety data from Arms 1-3 will support the process to select a dose for subsequent clinical development.

Although data from AI468002 Part C (in HIV-1 clade C infected subjects) was not included in the exposure-response assessment described above, BMS-955176 doses  $\geq 40$  mg SDD once daily demonstrated median maximal reductions in HIV-1 RNA  $> 1 \log_{10}$  in both clade B and clade C HIV-1 infected subjects (see [Section 1.4.1.3](#)); thus, doses of BMS-955176 60 mg, 120 mg, and 180 mg are expected to yield a similar response in HIV-1 infected subjects of either clade.

Table 1.1.2-1 depicts the projected exposure multiples of BMS-955176 60 mg, 120 mg, and 180 mg MC tablet with food at the NOAEL for pre-clinical findings of interest.

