## 4 STUDY DRUG

Study drug includes both Investigational [Medicinal] Product (IP/IMP) and Non-investigational [Medicinal] Product (Non-IP/Non-IMP) and can consist of the following:

| Table 4-1: Study Drugs for AI468038:        |                     |                      |                              |                                                                              |                                                                                      |
|----------------------------------------------------|---------------------|----------------------|------------------------------|------------------------------------------------------------------------------|--------------------------------------------------------------------------------------|
| Product Description / Class and Dosage Form | Potency      | IMP / Non-IMP | Blinded or Open Label | Packaging/ Appearance                                                 | Storage Conditions (per label)                                                |
| BMS-955176                                         | 60 mg a  | IMP                  | Blinded                      | Bottle/
A white to off-white, biconvex, oval shaped film coated tablet    | Store at 15 - 25°C

Protect from light.
Store in a tightly closed container |
| BMS-955176                                         | 120 mg a | IMP                  | Blinded                      | Bottle/
A white to off-white, biconvex, capsule shaped film coated tablet | Store at 15 - 25°C

Protect from light.
Store in a tightly closed container |
| Placebo to match
BMS-955176 60 mg a  | N/A                 | IMP                  | Blinded                      | Bottle/
A white to off-white, biconvex, oval shaped film coated tablet    | Store at 15 - 25°C

Protect from light.
Store in a tightly closed container |
| Placebo to match
BMS-955176 120 mg a | N/A                 | IMP                  | Blinded                      | Bottle/
A white to off-white, biconvex, capsule shaped film coated tablet | Store at 15 - 25°C

Protect from light.
Store in a tightly closed container |

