#### **4.1 Investigational Product**

An investigational product, also known as investigational medicinal product in some regions, is defined a pharmaceutical form of an active substance or placebo being tested or used as a reference in a clinical study, including products already with a marketing authorization but used or assembled (formulated or packaged) differently than the authorized form, or used for an unauthorized indication, or when used to gain further information about the authorized form.

The investigational product should be stored in a secure area according to local regulations. It is the responsibility of the investigator to ensure that investigational product is only dispensed to study subjects. The investigational product must be dispensed only from official study sites by authorized personnel according to local regulations.

In this protocol, investigational product(s) is/are: BMS-955176 and EFV. These products will be supplied.

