| Resistance Testing
(HIV-1 Drug Resistance)               |                                                      |                                                                                                                                                             |
| GenoSure                                             | X                                                    | Complete set of test results may take up to 4 weeks.                                                                                                        |
| PhenoSense Gag                                       | X                                                    |                                                                                                                                                             |
| Next Generation Seq. - Qs Gag                        | X                                                    |                                                                                                                                                             |
| Exploratory Resistance
(HIV-1 Drug Resistance)           | X                                                    | Molecular analysis at BMS WFD Discovery of baseline resistant samples and baseline sensitive controls in cases of subsequent on-treatment virologic failure |

a By definition, a pharmacodiagnostic sample (PDx) is a pre-treatment test to determine whether or not a patient is likely to respond to a drug (ie, a predictive test). Based on the results of clinical studies with BMS-955176, BMS may have to develop a PDx assay. Thus, PDx samples obtained at Screening in this study would be used for that sole purpose.

| Table 5.1-2: Short-term Procedural Outline (AI468038) |                                  |                                                                             |                                                                                                                              |                                                                             |                                                                                                             |                                                                                           |

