#### **5.4.2.2 Drug Resistance Testing**

Plasma samples for viral drug resistance testing will be collected at Screening for all subjects and the HIV-1 drug resistance genotype will be analyzed to rule out resistance to any component of the study regimen or specific resistance mutations as outlined in [Section 3.3.2](#), Exclusionary Criteria. At subsequent visits, samples for emergent drug resistance testing (both genotypic and phenotypic) will be collected and stored to be tested as outlined in [Section 5.4.1](#).

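### Exclusion 1a, read with the protocol's own definition of study drug, bars resistance to BMS-955176 at Screening, while Section 1.1.2 says enrolment does not depend on it

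*Protocol*

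**What the plan says.** Section 3.3.2, criterion 1a, and the matching Synopsis bullet exclude subjects with "Resistance or partial resistance to any study drug determined by tests at Screening". Section 5.4.2.2 says that the Screening genotype "will be analyzed to rule out resistance to any component of the study regimen", in addition to the specific mutations listed in Section 3.3.2.

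Section 4 defines study drug as the investigational and non-investigational products together. Section 4.1 adds: "In this protocol, investigational product(s) is/are: BMS-955176 and EFV". The Screening table (Table 5.1-1) lists "PhenoSense Gag" and next-generation Gag sequencing in the resistance-testing block.

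Section 1.1.2, on dose selection, states: "This Phase 2b clinical trial will enroll subjects regardless of their viral susceptibility to BMS-955176". It expects a spread of baseline EC90 values and argues that "the three doses above will give a wide range of exposures and coverage to assess against a range of baseline susceptibilities". Inclusion 2d requires full susceptibility to EFV, TDF and FTC and does not mention BMS-955176. Section 1.3.3 has an exploratory objective on how baseline Gag polymorphisms affect efficacy in Arms 1-3.

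**The concern.** One set of passages makes Screening resistance to BMS-955176 a reason for exclusion. The other says that susceptibility to it plays no part in enrolment. Both cannot govern eligibility, and Section 3.3.2 closes by insisting that every criterion be fully met.

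What is at stake is which population the trial describes. The three doses are justified partly by the wish to see them work against virus of differing susceptibility, and the Week 24 results feed the choice of Continuation Dose. If less susceptible virus is screened out, the dose assessment covers a narrower range than Section 1.1.2 promises, and the Gag objective loses some of its most informative subjects. The criterion also has no cut-off for full or partial resistance to BMS-955176, so two sites that took it seriously could apply it differently.

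**Working it through.** The point is textual. The one sample-size figure (Section 8.1) reproduces: 40 responders of 50 give an exact 95% interval of 66.3% to 90.0%, against the stated 66% to 90%. Nothing below depends on it.

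1. **Does 1a cover BMS-955176?** On the definitions, yes. Study drug means investigational plus non-investigational product (Section 4), and BMS-955176 is investigational (Section 4.1). Section 5.4.2.2 speaks of any component of the regimen, and BMS-955176 is one in Arms 1-3.

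2. **Could a Screening test trigger it?** A relevant one is collected. Table 5.1-1 places PhenoSense Gag and Gag sequencing under Screening resistance testing and notes that a complete set of results may take up to 4 weeks, which fits inside the 42-day screening period.

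3. **Does a narrow reading give 1a work to do?** Very little. Inclusion 2d already requires full susceptibility to EFV, TDF and FTC, which rules out partial resistance to them, and exclusions 1b-1e name specific mutations. The only drug 1a adds to that set is BMS-955176.

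4. **What contradicts it?** Section 1.1.2 (enrol regardless), inclusion 2d (three drugs only), Section 1.3.3 (baseline Gag variation is to be studied) and the absence of any Gag mutation from 1b-1f. Table 5.1-1 also plans exploratory work on baseline-resistant samples in cases of later on-treatment virologic failure. If that includes resistance to BMS-955176, it presupposes that such subjects were enrolled.

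5. **Clade AE.** Section 1.4.1.2 describes these isolates as about 2- to 3-fold less susceptible to BMS-955176. Section 3.1 nevertheless plans for up to about 16 such subjects (16/200 = 8%; 16/4 = 4 per arm) and stratifies on clade. With partial resistance undefined, 1a could bar some of a stratum the design deliberately admits.

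6. **Direction of effect.** Removing less susceptible virus could raise response in Arms 1-3. It should do little in Arm 4: Section 1.4.1.2 reports that approved drug classes, including NNRTIs, kept their potency against virus with reduced susceptibility to BMS-955176.

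7. **Size.** This would need the proportion of screened subjects falling below a cut-off and their response at each dose. The protocol gives no cut-off, no prevalence and no response rate by susceptibility, so no number follows.

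**The case against.** The best reply is that the intended meaning can be recovered. Inclusion 2d attaches the words study drugs to EFV, TDF and FTC. Exclusion 4a does the same twice, listing only those three even though BMS-955176 is investigational. Exclusions 1b-1d then name mutations for exactly those drugs. Section 5.4.2.2 ties eligibility to a genotype. Section 5.6 treats the Gag assays as biomarkers, analysed if judged clinically relevant, and Section 5.9 says biomarker results may be delayed or withheld from sites. A site cannot exclude on a result it never receives.

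Most of this stands. It makes the narrow reading the more probable intention and makes wide literal application less likely. It does not remove the conflict: no passage exempts BMS-955176 from 1a, Table 5.1-1 files the Gag assays under Screening resistance testing, and Sections 1.1.3 and 1.5 rely on three fully active or fully susceptible agents, which could lead a reader to the broad reading.

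Three stronger conclusions might be inferred and are not supported:

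- That 1a removes the very subjects the three doses are meant to test. Even literally, it removes one undefined tail of a range. Section 1.1.2 also reports that baseline EC90 was left out of the exposure-response model for lack of significance, though it was marginal and might matter with more data.
- That response in Arms 1-3 would be inflated by a stated number of points. Any such figure needs inputs the protocol lacks. The roughly 50% in Section 1.4.1.2 concerns polymorphisms and the first-generation drug, and the same section says BMS-955176 was developed to cover those variants better.
- That the comparison with EFV is biased. The exclusion acts before randomisation and equally on all arms. The effect is on whom the result describes, not on validity among those enrolled.

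**Conclusion.** The contradiction holds on the protocol's own definitions. Exclusion 1a, its Synopsis copy and Section 5.4.2.2 cannot be squared with Sections 1.1.2 and 1.3.3 and inclusion 2d. Followed literally, 1a would drop an unknown low-susceptibility fraction, possibly some clade AE subjects among them, and so narrow the range over which the doses and the Gag objective are assessed.

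A shift in favour of Arms 1-3 is possible in direction only. It assumes that sites receive and act on Gag results and that lower susceptibility lowers response; the protocol establishes neither. This is an inconsistency in a binding criterion, worth correcting because it is cheap to correct. It is not a flaw in the randomised design.

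**What to change.** Reconcile the passages in one amendment, following the stated enrolment intent:

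- Limit exclusion 1a and the Synopsis bullet to resistance or partial resistance to EFV, TDF or FTC.
- Align Section 5.4.2.2 to the same three drugs. Amending 1a alone would leave the broad rule standing there.
- Keep the specific mutations in 1b-1f unchanged.
- State, in Section 3.3.2 or 5.6, that Screening Gag genotype and phenotype results are not used for eligibility.

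If the sponsor does want a BMS-955176 susceptibility criterion, the protocol must instead give a cut-off and revise Sections 1.1.2 and 1.3.3 and inclusion 2d to match. The recommended change costs a few lines in about four places and leaves sample size, randomisation and analyses untouched.
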